### Sample size

Based on evidence of the results of previous clinical trials summarized in the systematic review, the pCR rate of nCRT alone is approximately 16% (5), and the pCR rate of nCRT combined with ICIs is approximately 36% (13). Therefore, this study sets the null hypothesis (H0) at P0 = 0.16 and alternative hypothesis (H1) at P1 = 0.36. Using a two-sided test with α = 0.05 and β = 0.2, and accounting for a 20% dropout rate, the calculated total sample size is 40 patients. Computations were performed using PASS 2021 v21.0.3.

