## Abstract

**Background:**

Neoadjuvant chemoradiotherapy has become the standard treatment for mid-to-low location LARC. Recently, total neoadjuvant therapy (TNT) has been used in patients with ‘high-risk’ or ‘very high-risk’ LARC according to ESMO guideline (2017). TNT not only increases the pathological complete response (pCR) rate, but also provides patients with more opportunities to preserve organ function. However, TNT mode seems to have reached a plateau. Some clinical studies published in recent years have also confirmed that different modes of neoadjuvant chemoradiotherapy combined with ICIs can further improve the pCR rate to varying degrees. It is necessary to explore an appropriate treatment mode for patients with mid-to-low location, who are unresectable or difficult to achieve R0 resection at the initial stage of surgery and have a strong desire to preserve anal cavity. Numerous basic researches have demonstrated that radiotherapy can remodel the tumor immune microenvironment and play a potential synergistic effect on ICIs. Therefore, this study will aim to explore whether TNT combined with ICIs could improve pCR rates in patients with ‘high-risk’ or ‘very high-risk’ LARC.

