## Background

Among all cancers, colorectal cancer ranks third in incidence and second in mortality worldwide (1). In China, the incidence of rectal cancer is on the rise, and most patients are diagnosed with locally advanced rectal cancer (LARC) at initial diagnosis (2), characterized by low rates of R0 resection and anal preservation (3). Preoperative neoadjuvant chemoradiotherapy (nCRT) has emerged as the standard treatment for mid-to-low location LARC (4). Statistical data indicates that nCRT achieves pathological complete response (pCR) rate of 8% - 24%, offering patients who achieved clinical complete response (cCR) potential ‘Watch and Wait’ opportunities (5–8). Preserving anal sphincter function while maintaining efficacy has become a key issue for LARC. Clinical trials demonstrate that total neoadjuvant therapy (TNT) can improve both pCR rates and organ preservation. However, in most trials, the pCR rate related to TNT was still lower than 30%, highlighting the need for novel strategies to enhance tumor response (9). The European Society for Medical Oncology (ESMO) guideline classify patients into different subgroups based on digital rectal examination (DRE), rectal high-resolution magnetic resonance imaging (HRMRI), and rectal intraluminal ultrasound (10). The guideline recommends adjusting treatment regimens for patients in different risk levels to achieve better efficacy and lower risk in precise treatment. While PD-1/PD-L1 inhibitors revolutionized care of colorectal cancer with deficient mismatch repair (dMMR) or microsatellite instability-high (MSI-H) phenotype, these represent only 8% - 10% of the cases. The remaining cases of proficient mismatch repair (pMMR) or microsatellite stabilization (MSS) phenotype could hardly benefit from immune checkpoint inhibitors (ICIs) treatment. Interestingly, it has been demonstrated that radiotherapy has the effect of stimulating the release of neoantigens and activating immunity (11). Building on this, the VOLTAGE study demonstrated that adding ICIs after nCRT could increase the pCR rate of MSS phenotype rectal cancer to 30% (12). At present, studies have shown that TNT combined with immunotherapy demonstrates better tumor regression and pCR rates, but its survival benefits such as DFS and OS need longer follow-up (13). Crucially, no solid evidence yet confirms whether adding immunotherapy significantly boosts pCR rates for mid-to-low location LARC patients with ‘high-risk/very high-risk’ according to ESMO guideline. Our center conducted a prospective, single-arm, observational study of long course concurrent chemoradiotherapy consolidation chemotherapy combined with PD-1 inhibitors, and the results are being submitted (STARS-RC03, NCT04906044). A total of 29 pMMR LARC patients received neoadjuvant long-course concurrent chemoradiotherapy followed by at least 3 cycles of CapeOX chemotherapy combined with PD-1 inhibitor. One patient discontinued treatment and was not effectively evaluated for efficacy. Our results showed that this regimen was safe and tolerated. Grade III toxicity was mainly associated with chemotherapy-induced hematological toxicity (51.71%, 15/29), and was reversed through active symptomatic treatment. No grade III or higher immunotherapy-related toxicity was observed. The pCR rate was 17.86% (5/28), and the overall complete response rate (cCR and pCR) was 50% (14/28). In 19 patients who undergone radical surgery, the major pathological remission (MPR) rate was 73.58% (14/19), and the R0 resection rate was 89.47% (17/19). Subgroup analysis found that the CR rate was positively correlated with the number of consolidation therapy, but the incidence of grades III or higher adverse events did not increase with the number of consolidation therapy. Building on these results, we propose the hypothesis that neoadjuvant long-course concurrent chemoradiotherapy sequential 6 cycles CapeOX regimen combined with PD-1 inhibitor further enhances the tumor pCR rate and has the potential to improve prognosis in mid-to-low location LARC patients with ‘high-risk/very high-risk’ and with pMMR phenotype.

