In recent years, the application of the TNT mode has gained traction, particularly in patients with refractory LARC. Phase III randomized controlled clinical studies have reported that TNT mode elevates the pCR rate of patients with LARC to 28%, the organ function preservation rate to 50%, and reduced the distant metastasis rate to 17% (15). TNT offers the advantage of more substantial tumor shrinkage, a significant increase in the cCR rate, and more opportunities for ‘Watch and Wait’. This approach preserves the structure and function of organs, ultimately enhancing the quality of life for patients with LARC (16). Moreover, the 7-year follow-up results of the PRODIGE-23 study (7), presented at the 2023 ASCO Annual Meeting, highlighted that the TNT regimen, consisting of three-agent, high-intensity induction chemotherapy combined with long-course concurrent chemoradiotherapy, not only enhanced the pCR rate (28% *vs*. 13%) but also conferred a long-term survival benefit. However, 43% of the study’s patient population had T2–T3b stage and 13% had high location rectal cancer (10–15 cm from the anal verge). This raises a cautious consideration regarding the necessity of high-intensity preoperative neoadjuvant therapy for patients with LARC without high-risk factors. In response to this question, the OPRA study specifically enrolled only patients with low LARC (17). The results hinted that the TNT mode, comprising neoadjuvant long-course concurrent chemoradiotherapy plus sequential full cycles consolidation chemotherapy, improved the de-operation survival rate for patients. The CAO/ARO/AIO-12 study further affirmed that consolidation of full cycles of chemotherapy after long-course concurrent chemoradiotherapy produced a higher pCR rate than induction approach (18). The precise stratification of neoadjuvant therapy for patients with LARC has become a pivotal topic in clinical multidisciplinary consultations. Currently, ICIs has been demonstrated to be effective in dMMR/MSI-H LARC, avoiding the toxicity of nCRT and radical surgery (19). This underscores the importance of precise adjustments in neoadjuvant therapy for patients with LARC.

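### Beating the 16% null shows only that the whole regimen outperforms chemoradiotherapy alone, not that sintilimab adds to total neoadjuvant therapy

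*Protocol article*

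**What the plan says.** The Sample size section of the protocol article gives the source of each rate. For the null, "the pCR rate of nCRT alone is approximately 16" per cent, and on that basis "this study sets the null hypothesis (H0) at P0 = 0.16". For the alternative, "the pCR rate of nCRT combined with ICIs is approximately 36% (13"), giving P1 = 0.36. The error rates follow: "Using a two-sided test with α = 0.05 and β = 0.2, and accounting for a 20% dropout rate", for a total of 40 patients. No test statistic or success cut-off is named.

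The regimen is described in the Abstract (Methods) and in Study design: 50 Gy long-course CRT with capecitabine, then six cycles of CapeOX with sintilimab. That is a TNT backbone with a PD-1 inhibitor added.

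The Abstract (Background) states the purpose: "this study will aim to explore whether TNT combined with ICIs could improve pCR rates" in high-risk or very high-risk disease. The Background section adds that solid evidence is lacking on whether immunotherapy raises pCR in this population.

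For TNT without an ICI, the article offers two figures. The Background section says "in most trials, the pCR rate related to TNT was still lower than 30" per cent. The Discussion says of phase III randomised studies that "TNT mode elevates the pCR rate of patients with LARC to 28" per cent.

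**The concern.** The null hypothesis and the scientific question use different comparators. H0 is CRT without consolidation chemotherapy. The question is what an ICI adds to CRT that already has consolidation chemotherapy. The alternative does not close the gap: the reference behind 36% is labelled CRT plus ICI in Sample size, but the Background cites the same reference for TNT combined with immunotherapy. Moving from 16% to 36% may therefore include the effect of the chemotherapy as well as that of the ICI, and a single-arm test cannot separate them.

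At stake is the meaning of a positive result. The 5% error rate protects the statement that the package beats 16%. It does not protect the statement that immunotherapy further raises pCR. A result that the backbone alone could produce might be reported as a benefit of immunotherapy.

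**Working it through.** **Inputs.** P0 = 0.16, P1 = 0.36, two-sided α = 0.05, power 80%, dropout 20%, N = 40 (Sample size). TNT without an ICI: 28% (Discussion), below 30% in most trials (Background). The centre's earlier study of CRT, at least three CapeOX cycles and a PD-1 inhibitor: 5/28 = 17.86% (Background).

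**Step 1: reproduce N.** One-sample proportion, normal approximation:

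n = [(1.96·√(0.16·0.84) + 0.8416·√(0.36·0.64)) / 0.20]² = 31.5, rounded up to 32.

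32 / (1 − 0.20) = 40. This matches the plan exactly.

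**Step 2: success rule.** The article names no test, so an exact binomial test with at most 2.5% in the upper tail is assumed. The cut-off is the smallest r with P(X ≥ r | n, 0.16) ≤ 0.025.

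- n = 32: r = 10, upper-tail error 0.0238, power at 0.36 = 76.9%.
- n = 40: r = 12, upper-tail error 0.0194, power at 0.36 = 83.0%.

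**Step 3: chance of a positive result if sintilimab adds nothing.** This is P(X ≥ r | n, p), where p is the true pCR rate of the backbone alone in this population.

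| True rate p | n = 32 (≥10) | n = 40 (≥12) |
|---|---|---|
| 17.86% | 4.7% | 4.2% |
| 20% | 9.0% | 8.8% |
| 25% | 26.3% | 28.5% |
| 28% | 40.5% | 44.8% |
| 30% | 50.5% | 55.9% |

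The test also matters. With an uncorrected z-test the cut-off at n = 32 is still 10, but at n = 40 it falls to 11 (z = (0.275 − 0.16)/√(0.16·0.84/40) = 1.98). The chance at 28% is then 58.8%.

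**Step 4: what would support a claim over TNT.** Require the exact (Clopper-Pearson) 95% lower limit to exceed 28%.

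- n = 40: 18/40 has lower limit 29.3% and qualifies; 17/40 has 27.0% and does not.
- n = 32: at least 15/32, since P(X ≥ 15 | 32, 0.28) = 0.0177, while 14/32 gives 0.041.
- Chance of meeting this rule at a true 36%: 13.7% (n = 32) and 15.4% (n = 40).

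**Step 5: cost of changing the null instead.** With P0 = 0.28 and P1 = 0.36, the formula in step 1 has a difference of 0.08 and gives 257.6, so 258 evaluable patients and 258/0.80 = 322.5, rounded up to 323 enrolled.

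**The case against.** The other side has four good arguments.

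- **The benchmark may not transfer.** The Discussion itself notes that one trial reporting 28% had 43% T2–T3b disease and 13% high tumours, and used three-agent induction chemotherapy. This trial takes only higher-risk tumours within 10 cm. The figure below 30% is a ceiling for most trials, not an estimate.
- **Watch-and-wait lowers the observable rate.** Study endpoints and assessment keeps unoperated complete responders in the modified intention-to-treat set. Suppose that 28% applies only to operated patients, that the operated share is 19 of 28 as in the earlier study, and that unoperated patients count as failures. The observable rate is then 0.28 × 19/28 = 19%, and the chance of a positive result is 6.8% (n = 32) or 6.4% (n = 40).
- **The formal aim is modest.** Study design says the trial will assess the pCR rate of the whole regimen, and the article calls CRT the standard. Testing a new package against the standard is an ordinary phase II choice.
- **Changing the null is costly.** Step 5 shows that 40 patients cannot test 28% against 36% with useful power, and enrolment has been open since October 2023.

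All four stand as limits on the size of the problem and on the remedy. None makes rejection of 16% informative about what sintilimab adds to TNT. If the investigators expect TNT alone to give about 16% in this population, the article does not say so, and the figure it cites is 28%.

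A reader might infer that an inactive sintilimab would be declared a success 40% to 45% of the time. The document does not support that as an unconditional statement: it holds only if 28% carries over and the test is exact. A reader might also infer that the sample size is wrong or that P0 = 0.16 is invalid. Neither follows. N reproduces, and 16% is a legitimate null for the narrower question.

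**Conclusion.** The concern holds as a limit on interpretation. The null is CRT alone, the regimen is TNT plus an ICI, and the stated question is the ICI's contribution. A rejected H0 supports superiority of the package over CRT alone and nothing further.

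The size depends on the unknown TNT-alone rate in this population. Assuming an exact test and no sintilimab effect, the chance of a positive result runs from 4–5% at 17.86% to 51–56% at 30%, with 40–45% at the article's own 28%. The 17.86% is a reference point only, because that earlier regimen already contained a PD-1 inhibitor.

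**What to change.** Keep P0 = 0.16 and N = 40 for the primary test, and make three changes in wording.

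1. In Sample size, the Abstract and the Discussion, state that rejecting H0 supports only a higher pCR rate than CRT alone.
2. Prespecify, before results are known, that any statement that sintilimab adds to TNT requires the lower limit of the exact 95% confidence interval for pCR to exceed 28%. That means at least 15 of 32 or 18 of 40. Add that it would still be a comparison across trials.
3. State that the chance of meeting this rule at a true rate of 36% is only about 14% to 15%.

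No extra patients are needed and the primary hypothesis is unchanged during enrolment. The cost is a narrower claim and an openly low power for the ICI question. Resetting P0 to 0.28 is not recommended at this sample size: it would leave the primary test with the same 14% to 15% power at the plan's own P1.

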### Study endpoints and assessment

The primary endpoint of this trial is the pCR rate, defined as the percentage of patients who achieved pCR after nCRT in the eligible population. Secondary endpoints include 2-year sustained of cCR rate; CR rate (the rate of patients with sustained cCR for 2 years and pCR); MPR, which is defined as residual viable tumor (RVT) ≤10%; neoadjuvant rectal (NAR) score, which were calculated based on pathological and clinical staging (NAR=[5pN - 3(cT - pT) + 12]^2^/9.61); 3-year non⁃regrowth disease free survival; 3-year disease-free survival; 3-year overall survival; 3-year localized recurrence-free survival; 3-year distant metastasis free survival; 3-year stoma-free survival, anal sphincter preservation rate; surgical R0 resection rate and safety (adverse events during neoadjuvant therapy and 30 days after surgery, as well as tolerance). In addition, the study also has exploratory endpoints to further investigate potential factors related to antitumor therapy, such as infiltrating lymphocytes in tumor tissue, the structure of gut microbiome, and RAS/BRAF status.

The per-protocol set (PP) is defined as subjects who strictly adhered to the study protocol without major violations, completed all treatment and follow-up, and had measurable data for the primary endpoint (pCR). The modified intention-to-treat set (mITT) excludes participants who received no intervention or provided absolutely no post-baseline data. Patients achieving cCR who opt for Watch & Wait management are included in the mITT set for efficacy analysis.

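### N = 40 reproduces, but its 80% power is nominal: attained power is about 77% with 32 evaluable patients, and lower if treated dropouts stay in the denominator

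*Protocol article*

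**What the plan says.** The Sample size section of the protocol article gives all the planning inputs. On the hypotheses, "this study sets the null hypothesis (H0) at P0 = 0.16 and alternative hypothesis (H1) at P1 = 0.36". On the error rates: "Using a two-sided test with α = 0.05 and β = 0.2". On the total: "accounting for a 20% dropout rate, the calculated total sample size is 40 patients". The software is named ("Computations were performed using PASS 2021 v21.0.3"), but not the test, nor whether the calculation was exact or approximate.

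The section Study endpoints and assessment gives the primary endpoint as pCR, "defined as the percentage of patients who achieved pCR after nCRT in the eligible population". It then defines two analysis sets. The per-protocol set is limited to adherent completers with a measurable pCR result. The mITT set is much wider: it "excludes participants who received no intervention or provided absolutely no post-baseline data". Neither set is named as primary, neither is linked to the sample size, and no rule is given for a treated patient who never yields a pCR result.

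**The concern.** There are two separate issues.

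First, the plan states β = 0.2, but with about 32 binary outcomes the rejection cutoff moves in whole patients. The power actually attained can differ from what a smooth formula returns.

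Second, dividing 32 by 0.8 restores the planned information only if the 20% who drop out are removed from the analysis. A set that removes only untreated patients and those with no post-baseline data would keep many of them. The section on discontinuing or modifying interventions describes patients of this kind: those who cannot tolerate consolidation or who progress are discussed by the multidisciplinary team and remain in follow-up. A patient kept in the denominator without a pCR pulls the observed rate down, which extra enrolment does not offset.

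At stake is the reading of a negative result. The plan implies a 20% risk of missing a true 36% rate. If the real risk is larger, a non-significant result says less against the regimen than readers would assume.

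**Working it through.** **Inputs.** P0 = 0.16, P1 = 0.36, two-sided α = 0.05, β = 0.2, dropout 20%, N = 40 (all from Sample size). Analysis sets are from Study endpoints and assessment.

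**Step 1: reproduce the plan's figure.** One-sample z-test with the null variance:

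n = [(1.96·√(0.16·0.84) + 0.8416·√(0.36·0.64)) / 0.20]²
= [(0.7185 + 0.4040) / 0.20]² = 31.5, rounded up to 32.

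Inflation: 32/0.8 = 40, an exact match. Nominal power at n = 32 is Φ[(0.20·√32 − 0.7185)/0.48] = 80.5%. There is no arithmetic slip.

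**Step 2: attained power at 32 evaluable patients.**
- z at 9/32 is (0.28125 − 0.16)/√(0.1344/32) = 1.87, not significant; at 10/32 it is 2.35. The z-test rejects upward at ≥10.
- Exact test with 0.025 in the upper tail: P(X ≥ 10 | 32, 0.16) = 0.0238, so again ≥10.
- Power: P(X ≥ 10 | 32, 0.36) = 76.9%, about 3 points below 80%.

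**Step 3: what happens if dropouts are retained.** Three assumptions are needed that the article does not state: mITT is the primary set; 36% is the rate among evaluable patients; and a retained dropout has no pCR. If all 8 are retained, the expected rate is 0.8 × 0.36 = 0.288 with n = 40. If 4 are retained, it is 0.36 × 32/36 = 0.32 with n = 36.

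At n = 40 the two tests part. z at 11/40 is (0.275 − 0.16)/√(0.1344/40) = 1.98, so the z-test rejects at ≥11. The exact test needs ≥12.

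| Scenario | n, rate | Test | Cutoff | Upper-tail error at 0.16 | Power |
|---|---|---|---|---|---|
| All 8 excluded | 32, 0.36 | both | ≥10 | 2.4% | 76.9% |
| 4 retained | 36, 0.32 | both | ≥11 | 2.2% | 63.5% |
| All 8 retained | 40, 0.288 | exact | ≥12 | 1.9% | 49.3% |
| All 8 retained | 40, 0.288 | z | ≥11 | 4.5% | 63.1% |
| No dropouts | 40, 0.36 | exact | ≥12 | 1.9% | 83.0% |
| No dropouts | 40, 0.36 | z | ≥11 | 4.5% | 90.3% |

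Holding the evaluable number fixed at 32, instead of diluting the rate, changes little: P(X ≥ 12 | 32, 0.36) = 49.6% and P(X ≥ 11 | 32, 0.36) = 64.0%.

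The z-test's higher power at n = 40 comes with an upper-tail error of 4.5% against a nominal 2.5%.

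**The case against.** The strongest reply is that the calculation is standard and correct by its own method, and that 32 happens to be an unlucky number. This is largely right. The same z-test attains 80.8% at n = 30 and 80.5% at n = 33, so 76.9% is a local trough caused by discreteness, and the evaluable count need not be exactly 32. Two things remain: 32 is the number the plan itself aims at, and the z-test's upper-tail error at those neighbours is 4.0% and 2.9%, above the nominal 2.5%. An exact-test target can be quoted too (the 2.5% upper-tail version first reaches 80% at n = 36, or 45 after inflation), but it is specific to that version. A two-sided exact test ordered by likelihood reaches 80.8% at n = 30. It is no benchmark the plan failed to meet.

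The second reply concerns the dropouts. A reader might infer that the inflation and the analysis set flatly contradict each other, and that true power is about 49%. The documents do not support that. Nothing makes mITT primary, nothing counts dropouts as non-pCR, and the per-protocol set fits the inflation. Some dropouts would leave mITT anyway, because they were untreated or had no post-baseline data. Patients referred to the multidisciplinary team are not called dropouts, nor are they excluded from surgery. If the 36% taken from the cited review is already a rate among all treated patients, diluting it counts the loss twice. And 49% belongs to the exact test; the z-test that yields N = 40 gives 63%.

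The centre's own earlier study, described in the Background, points both ways. pCR was reported as 5/28 although 19 were operated on, so 9 unoperated patients stayed in; one patient who discontinued without evaluation was left out (29 to 28).

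The third reply is that the test, missing-outcome rule and cutoff are commonly left to an analysis plan. That stands: their absence from an article is not itself a fault. The point here is that the power figure the article does state depends on them.

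**Conclusion.** The point holds in a limited form. N = 40 is correctly derived by a normal approximation; the 80% attached to it is nominal. At the planned 32 evaluable patients the attained power at 36% is 76.9%, a shortfall of about 3 points that needs no assumption about dropouts beyond their exclusion and is the same for the z-test and the exact test.

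The larger loss is conditional. Under the three assumptions in the working, with all 8 dropouts retained, power is about 49% (exact) to 63% (z). Under the same assumptions with half of them retained, it is 63.5%. With no dropouts it exceeds the target, at 83% or 90%. The article does not settle which case applies, so the supportable statement is a range tied to its conditions. Neither a wrong sample size nor a power of one half has been shown.

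**What to change.** Keep N = 40 and reword the Sample size paragraph:

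- Say that 40 comes from a normal approximation with nominal power of 80%.
- Name the test, the primary analysis set and the cutoff in numbers of pCRs, and say how a treated patient without a pCR result is counted.
- Give the attained power under that choice: about 77% with 32 evaluable patients and dropouts excluded; about 49% (exact, ≥12 of 40) or 63% (z-test, ≥11 of 40) if all 8 dropouts are retained as non-pCR. If the z-test is chosen, report its 4.5% upper-tail error at n = 40.
- State whether the 36% is a rate among evaluable or among all treated patients.

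The cost is a change of wording and a less favourable stated power. No extra patients are needed. Enrolment is ongoing, so the choices should be fixed before the results are analysed, because the set and test decide whether 10, 11 or 12 pCRs count as success.
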